# Intermittent versus continuous esketamine infusions for long-term pain modulation in complex regional pain syndrome: protocol of a randomized controlled non-inferiority study (KetCRPS-2)

**DOI:** 10.1186/s12891-023-06258-4

**Published:** 2023-03-29

**Keywords:** CRPS, Complex regional pain syndrome, Inpatient, Outpatient, Esketamine, Ketamine, KetCRPS-2, Study protocol

## Abstract

**Background:**

Complex regional pain syndrome (CRPS) is a chronic pain condition of an extremity. While achieving pain relief in CRPS is challenging, esketamine infusions can accomplish pain relief for several weeks post-infusion in a subgroup of CRPS patients. Unfortunately, CRPS esketamine protocols are very heterogeneous in advice on dosage, administration and treatment setting. Currently, no trials are available that study differences between intermittent and continuous esketamine infusions for CRPS. With the current situation of bed shortages, it is difficult to admit patients for several consecutive days for inpatient esketamine treatments. In this study, we investigate whether 6 intermittent outpatient esketamine treatments are not inferior to a continuous 6-day inpatient esketamine treatment in establishing pain relief. In addition, several secondary study parameters will be assessed in order to investigate mechanisms responsible for pain relief by esketamine infusions. Furthermore, the cost-effectiveness will be analyzed.

**Methods:**

In this RCT, the primary objective is to demonstrate that an intermittent esketamine dosing regimen is non-inferior to a continuous esketamine dosing regimen at 3 months follow-up. We will include 60 adult CRPS patients. The inpatient treatment group receives a continuous intravenous esketamine infusion for 6 consecutive days. The outpatient treatment group receives a 6-hour intravenous esketamine infusion every 2 weeks for 3 months. Esketamine dose will be individually tailored and is started at 0.05 mg/kg/h and can be increased to a maximum of 0.2 mg/kg/h. Each patient will be followed for 6 months. The primary study parameter is perceived pain intensity, measured by an 11-point Numerical Rating Scale. Secondary study parameters are conditioned pain modulation, quantitative sensory testing, adverse events, thermography, blood inflammatory parameter, questionnaires about functionality, quality of life and mood and costs per patient.

**Discussion:**

If our study reveals non-inferiority between intermittent and continuous esketamine infusions, these findings can be beneficial to increase the availability and flexibility of esketamine infusions through outpatient treatments. Furthermore, the costs of outpatient esketamine infusions could be lower than inpatient esketamine infusions. In addition, secondary parameters may predict response to esketamine treatment.

**Trial registration:**

ClinicalTrials.gov Identifier NCT05212571, date of registration 01-28-2022.

Protocol version: Version 3, February 2022.

**Supplementary Information:**

The online version contains supplementary material available at 10.1186/s12891-023-06258-4.

## Background

Complex regional pain syndrome (CRPS) is described by the International Association for the Study of Pain (IASP) as “a syndrome characterized by a continuing regional pain that is seemingly disproportionate in time or degree to the usual course of pain after trauma or other lesion. The pain is regional and usually has a distal predominance of abnormal sensory, motor, sudomotor, vasomotor, edema and/or trophic findings” [1]. CRPS can have a severe impact on quality of life of patients and can lead to substantial physical as well as social disability [2]. When treating CRPS, the most prominent pathophysiological mechanisms of CRPS should be targeted in an individually tailored manner [3]. Several underlying pathophysiological mechanisms of CRPS have been implicated such as inflammation, peripheral and central sensitization, vasomotor disturbances and motor disturbances [3].

A pharmacotherapeutic option for targeting the pathophysiological mechanism central sensitization in CRPS is the dissociative anesthetic ketamine [3]. Ketamine is a racemic mixture of the enantiomers R-ketamine and S-ketamine (esketamine). Esketamine is preferred in the management of CRPS as esketamine possesses respectively twofold and fourfold stronger anesthetic and analgesic properties than R-ketamine and racemic ketamine [4, 5]. Evidence suggests a part of the analgesic effect of esketamine is mediated by antagonizing N-methyl-D-aspartate (NMDA) receptor activation and thereby influencing sensory processing disturbances [3, 6]. Some studies have also attributed immunoregulatory effects to esketamine [7–9]. Therefore, esketamine may inhibit the inflammatory pathophysiological mechanism of CRPS.

The effects of esketamine on pain relief in CRPS patients have been reviewed by Zhao et al. [10]. The investigators concluded that intravenous esketamine therapy for CRPS can provide effective pain reduction for up to 3 months post infusion in a subgroup of CRPS patients [10]. Unfortunately, CRPS literature contains a wide range of esketamine dosing regimens with the result that clinical protocols on dosage and administration are very heterogeneous [5, 10, 11].

In the Netherlands, CRPS patients are treated according to the Dutch guideline for CRPS [12]. This guideline recommends esketamine treatment when the pain is severe (Numerical Rating Scale ≥7) and other more conservative therapies have failed. Both outpatient and inpatient esketamine treatments are offered in the Netherlands [5]. The clinical protocol of our Center for Pain Medicine is a 6-day inpatient admission for continuous esketamine administration, with almost 50% of the patients still reporting pain relief 4 weeks after treatment [13]. Unfortunately, bed shortages and financial boundaries limit inpatient esketamine infusions. In addition, the COVID-19 pandemic showed that hospital bed capacity is limited and esketamine infusions for CRPS have been postponed or cancelled due to the scarcity of hospital beds and health care professionals during the pandemic. Esketamine infusions in an outpatient setting might increase flexibility and availability of esketamine treatment and may reduce costs. However, differences between intermittent and continuous esketamine infusions for CRPS have never been compared in randomized controlled trials (RCTs). To study this, we will conduct a non-inferiority RCT to assess whether a series of intermittent esketamine infusions, in 3 months every 2 weeks a day-care outpatient infusion of 6 hours, is non-inferior to a 6-day inpatient admission with continuous esketamine administration in establishing pain relief in CRPS patients. In addition, in both treatment settings, several objective parameters will be assessed to investigate mechanisms responsible for pain relief. Hopefully, this will lead to the identification of predictors of response to esketamine and in the future CRPS patients will be selected for esketamine treatment in a mechanism-based manner. Furthermore, the results of this study will include a cost-effective analysis. This study will help to guide decisions about the use of esketamine treatment for CRPS patients.

## Methods

### Ethics

Ethical approval for this study was obtained from the local Medical Ethics Committee (MEC-2021-0426). The EudraCT number is 2021-000640-21. The trial is registered in the Clincialtrials.gov registry (NCT05212571). Important protocol modifications will be reported to the local Medical Ethics Committee. Eligible patients can participate in the study after informed consent is obtained. Additional consent is requested for collection and use of participant data and biological specimens in future studies in the informed consent form. All data will be handled confidentially according to the General Data Protection Regulation.

### Study setting

The Center for Pain Medicine is a tertiary referral pain center specialized in the diagnosis and treatment of CRPS. The setting of the study will be in the outpatient clinic of the Center for Pain Medicine or the inpatient ward at the Center for Pain Medicine.

### Eligibility criteria

In order to be eligible to participate in this study, patients must meet the new IASP diagnostic criteria for CRPS [14] or must have met the new IASP diagnostic criteria of CRPS in the past (‘CRPS with Remission of Some features’) [15]. Inclusion criteria are age ≥ 18 years, CRPS in one upper extremity and/or CRPS in one lower extremity, esketamine treatment in an elective setting (i.e. not in an emergency setting), adequate comprehension of the Dutch language and willingness and ability to participate in the study. Patients are selected for an intravenous esketamine treatment by their treating pain specialist according to the Dutch CRPS guidelines [12]. Patients must suffer severe pain and/or therapy-refractory CRPS (i.e. when other more conservative treatments have failed).

Contraindications to participate in this study are based on the United States (US) consensus guidelines on the use of intravenous ketamine infusions for chronic pain [16]: severe liver disease, schizophrenia, psychosis, delirium, manic depression, active substance abuse, intoxication with alcohol or other substances, poorly controlled hypertension, unstable angina, high-risk coronary vascular disease, heart failure, elevated intracranial pressure, elevated intraocular pressure, thyrotoxicosis, pregnancy. Furthermore, use of derivatives of xanthine (such as theophylline) or ergometrine are contraindicated because of interactions with esketamine. For each patient, the contraindications and precautions for use of esketamine infusions will be assessed by their treating pain specialist.

### Recruitment, allocation and blinding

CRPS patients who are selected for a treatment with intravenous esketamine will be placed on the regular clinical waiting list of the Center for Pain Medicine. Patients will be selected chronologically from this waiting list for esketamine treatment and are contacted by a researcher for trial information. The expected duration of the study inclusion period will be approximately 3 years. The first patients will be included in 2022. Patients can withdraw from the study at any time without giving reasons. This is without any consequences for further medical treatment. Patients who are not willing to participate in this study will receive standard care (inpatient esketamine infusions).

After informed consent, patients will be enrolled and randomized using Castor software (Castor EDC). Previous treatments with esketamine may influence the outcomes of this clinical trial and therefore stratified randomization is performed with randomization blocks according to whether patients received previous esketamine treatment. The randomization will be done with an allocation ratio 1:1. The patients, researchers and statistician will not be blinded during the data collection and analysis. The researcher will enroll patients and will assign patients to the interventions after randomization.

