### Outcomes

The primary outcome parameter is perceived pain intensity measured by Numerical Rating Scale (NRS) at T3 and will be compared to the baseline NRS pain scores (T0). The NRS ranges from 0 (no pain) to 10 (worst pain imaginable). Both the current NRS pain score and the average NRS pain score of the last 24 hours will be asked during all study visits.

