### Statistical methods

Descriptive statistics are used to determine the frequency distributions of demographic variables, and to describe measures of central tendency and of dispersion, dependent on the shape of their distribution. The Shapiro-Wilk test is used to analyze whether or not continuous parameters are normally distributed. The effects of the treatment on the different study parameters will be evaluated with regression models to account for the stratification factor, received esketamine treatment in the past, in the randomization process. Continuous outcomes will be analyzed with a linear regression model, where the residuals will be evaluated for normality. In case of a violation of the assumption, (logarithmic) transformations will be applied. Count outcomes will be analyzed with Poisson regression models and binary outcomes with logistic regression models. For repeated measurements mixed effects, models will be used to account for correlations from measurements within the same patient. No correction of the rejection zone will be made for multiple comparisons, because of the more explorative nature of the analyses of the secondary and other parameters. All analyses will be conducted in accordance with the intention-to-treat principle. Data will be analyzed using the latest version of SPSS and R.

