The strengths of this study design are the randomized design and the stratification of patients based on whether they have had esketamine infusions in the past. Another strength of this study is that several objective parameters for esketamine treatments and the cost-effectiveness are assessed. Complementary to further understandings of esketamine mechanisms, diagnostic tests and biomarkers are needed to predict response on esketamine infusions for CRPS patients [13, 27, 53]. By incorporating a peripheral blood inflammatory parameter, conditioned pain modulation, thermography and QST, our research group hopes to provide information on differences between responders and non-responders to esketamine treatment. This paves the way to a more mechanism-based approach in selecting CRPS patient for esketamine treatment. A potential pitfall of the study protocol is that, although CRPS is a multi-mechanism syndrome, patients receive esketamine as a monotherapy. Targeting only a single mechanism might not be sufficient in CRPS [3]. Furthermore, patients cannot be blinded for an intermittent or continuous esketamine treatment. Of note, although the decisions of our research group on the treatment protocols for esketamine administration have been made after thorough consideration, significant uncertainty exists for the most ideal treatment regimen for esketamine infusions and may also differ for each individual CRPS patient. We acknowledge that all decisions on the length and dose of esketamine administration can influence the outcome parameters in this RCT.

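### The protocol leaves the statistician unblinded during analysis without giving a reason, while a transformation of a raw-scale non-inferiority outcome is still to be decided on the data

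*Protocol article*

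**What the plan says.** The section on recruitment, allocation and blinding states: "The patients, researchers and statistician will not be blinded during the data collection and analysis". This is a positive statement that covers the analysis stage and names the statistician separately from the researchers.

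The only justification is in the Discussion: "patients cannot be blinded for an intermittent or continuous esketamine treatment". No reason is given for the statistician. The article describes no coded-arm analysis, masked data review or independent analyst.

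On the model, Statistical methods says: "Continuous outcomes will be analyzed with a linear regression model, where the residuals will be evaluated for normality". It continues: "In case of a violation of the assumption, (logarithmic) transformations will be applied". A Shapiro-Wilk test is named for continuous parameters in general. No threshold is tied to the residuals, and the word 'logarithmic' stands only in brackets. The model is one of the "regression models to account for the stratification factor, received esketamine treatment in the past, in the randomization process".

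On the outcome, the Outcomes section defines the primary parameter as pain intensity on the NRS at T3, set against T0, and adds: "Both the current NRS pain score and the average NRS pain score of the last 24 hours will be asked during all study visits". It does not say which of the two scores is primary. The Sample size section puts the limit at −1.0 on the NRS.

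**The concern.** Patients must know their regimen, and so must those who treat them and the researchers who assign them. The analyst need not. The trial is open-label and its primary outcome is the patient's own rating, so masking the analyst is one of the few protections against bias still available. The plan gives it up.

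This would matter little if nothing were left to judgement, but the transformation rule is conditional on the data and has no criterion. An analyst who sees the arms can also see, while judging the residuals, which scale favours non-inferiority. Even if the judgement is made honestly, readers of the result cannot tell that it was. What is at stake is the credibility of the non-inferiority conclusion.

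**Working it through.** **1. The plan's own figure, and whether masking affects it.** Inputs from Sample size: margin 1.0, SD 1.5, true difference 0, power 80%.
- Per arm, n = 2 × SD² × (z_α + z_β)² / margin².
- One-sided α 0.05: 4.5 × (1.645 + 0.842)² = 27.8, so 28 per arm and 56 in total, as stated.
- One-sided α 0.025: 4.5 × (1.960 + 0.842)² = 35.3, so 36 per arm and 72 in total.
- With 60 patients, power is 82.6% at one-sided 0.05 and 73.3% at 0.025.

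The gap between the two levels is a separate matter. None of these figures depends on who knows the arm, so masking the statistician costs no patients.

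**2. Does the primary analysis need an identified arm?** It needs NRS at T0 and T3, prior esketamine treatment (the stratification factor) and an arm label. None of the first three identifies the regimen. Infusion-session records (T1A only versus T1A–F), dose and costs would identify it, but the primary model uses none of them.

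**3. Why the transformation step matters here.** A margin of 1.0 raw point has no single equivalent on a log scale. It is a ratio of 7/6 = 1.17 at a mean of 6.0 (the expected value at 3 months), 9/8 = 1.125 at a mean of 8.0, and 5/4 = 1.25 at a mean of 4.0. The scale also includes 0, where the logarithm does not exist, so an offset would have to be chosen. Deciding to transform therefore also means deciding what the margin becomes.

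**4. Can the residual check be done without the arm label?** Yes. Suppose the arms differ by the full margin, with SD 1.5 within each arm. The pooled data are then an equal mixture of two normals 1.0 apart. The variance is 2.25 + 0.25 = 2.5, and the excess kurtosis is −2 × 0.5⁴ / 2.5² = −0.02. Leaving the arm out of the model barely changes the shape being judged.

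**5. Can the harm be sized by simulating free choice among analyses?** Set-up: 30 per arm, SD 1.5, true deficit exactly 1.0, one-sided 0.025. The assumed correlations (not in the document) are 0.6–0.9 between current and 24-hour NRS and 0.3–0.5 between T0 and T3. The four analyses are the two scores, each as T3 value or as change from T0.

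| Analyst's behaviour | False non-inferiority |
|---|---|
| One fixed analysis | about 2.4% |
| Best of four, arms known | 5.9–7.7% |
| Best of four, arms coded A/B | 5.7–7.6% |

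Coding removes almost none of the rise. In a non-inferiority trial a small A–B difference is favourable whichever arm is which, so an analyst who sees A–B results can pick it without the code. The rise comes from analyses not being fixed in advance. What protects is fixing them before any between-arm result is seen.

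**The case against.** The strongest objection is that the harm comes from missing pre-specification. If the score, outcome form and transformation rule are fixed beforehand, an unblinded statistician has little left to influence; if they are free, A/B coding does not help. The simulation bears this out, so this part stands. It rules out any numerical claim and any remedy based on coding alone.

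Two stronger readings are tempting, and the document supports neither.
- A reader might infer that unblinding the statistician raises the false non-inferiority rate from about 2.4% to 6–8%. Those figures describe an analyst who always reports the best of four results. They are a worst case under assumed correlations, are nearly the same with coded arms, and do not include the transformation step.
- A reader might infer that the NRS version, or the choice between T3 value and change, is planned to be made after seeing data. Nothing says so. The article is silent on these details, and the full protocol or an analysis plan may fix them. The term 'average NRS pain score' in Sample size may mean the 24-hour item, or only the group mean.

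It can also be said that judging residual shape does not require knowing the arm. That is true, and it means the step can be done masked at no loss. Finally, masking is not free: the article reserves the final data set to the researchers and describes no separate unit to hold a code. The cost is therefore small rather than nil.

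The objection does not remove the sentence itself. An unseen analysis plan could add rules, but it could not have a masked statistician without contradicting what the protocol states.

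**Conclusion.** The point holds as a modest, inexpensive improvement. The protocol expressly leaves the statistician unblinded during analysis, gives a reason that applies only to patients, and keeps a data-dependent transformation step with no criterion against a margin set in raw NRS points. Its effect on the error rate cannot be quantified from the document, and no figure should be attached to it. The conclusion assumes that the primary analysis uses only T0 and T3 NRS, the stratification factor and the arm. It also assumes that no one has yet fixed the transformation decision elsewhere; if an analysis plan does so, the remaining risk is smaller, but the masking sentence would still be worth changing.

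**What to change.** Replace the blinding sentence with:

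*Patients and researchers cannot be blinded. The statistician fixes and signs off the NRS version, outcome form, model and any transformation decision before seeing any between-arm result, using data without an arm label; a coded arm label is then added, the primary analysis is run, and the code is opened afterwards.*

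Add that records revealing the regimen (T1 sessions, dose, costs) are linked only after the primary analysis. The order is essential: coding the arms while the choices are still open would achieve almost nothing.

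The cost is a label-free export followed by a coded one, prepared by someone other than the statistician, and a dated sign-off. The number of patients, visits and treatment do not change.

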### Participant timeline

During this study, endpoints will be assessed at baseline (T0), during inpatient and outpatient esketamine treatments (T1), the day after each hospital admission (T2) and at 3 months (T3) and 6 months (T4) after the first esketamine infusion. The intermittent 6 outpatient esketamine treatments are addressed with T1A, T1B, T1C, T1D, T1E and T1F. The continuous inpatient treatment is addressed with T1A. Figure 1 provides the flowchart of the study. Furthermore, Table 1 presents an overview of schedule of enrolment, interventions and assessments according to standard protocol items recommendations for interventional trials (SPIRIT) during the entire course of this study [17, 18]. All visits and interventions will be discussed in detail below.

**Fig. 1 Fig1:**
[figure not shown]
Detailed flowchart of the KetCRPS-2 study *Abbreviations: Complex Regional Pain Syndrome (CRPS), Numerical Rating Scale (NRS), Global Perceived Effect*
*(GPE), the Core Outcome Measure**ment set for complex regional PAin syndrome Clinical sTudies (COMPACT*)

**Table 1 Tab1:** Overview of schedule of enrolment, interventions and assessments in the KetCRPS-2 study. *According to Standard Protocol Items Recommendations for International Trials (SPIRIT)* [17, 18]

TIMEPOINT	STUDY PERIOD						
	Enrolment	Allocation	Post-allocation				Close-out
	***-t***_***2***_	***-t***_***1***_	***T0***	***T1A-F***	***T2A-F***	***T3***	***T4***
